#### Usual care

Participants in all three groups will receive usual care in addition to the allocated airway clearance intervention. Usual care will consist of medical therapy, prescribed by the patient’s treating physician (including antibiotics, corticosteroids, supplemental oxygen with or without humidification, nebulised medication), nursing care, and other allied health assessment and intervention as required. No other ACTs will be delivered as part of usual care. In the event of an emergency or significant clinical deterioration, the ward physiotherapist may treat the participant as they deem necessary, and the participant will then be returned to the allocated intervention when safe to do so. Any such instances will be recorded and reported. If a participant was treated with an alternative ACT for more than 48 h during their hospital admission, they will be excluded from secondary per-protocol analyses of the trial but included in the primary intention-to-treat analyses.

As part of usual care, all participants will receive a physical exercise training regimen based on ground-based walking, prescribed by the ward physiotherapist with the aim of returning to previous levels of function throughout admission [36, 39]. During this activity, participants will be monitored with the goal to maintain clinically acceptable, individually determined blood oxygen saturation levels and heart rate range parameters.

#### Group 1: the ACBT

Participants will complete the ACBT according to guidelines [24, 52], positioned sitting upright in a chair (or sitting up in bed if unable to sit in a chair). The ACBT consists of three components: breathing control, thoracic expansion exercises and forced expiratory technique (FET). The cycle implemented will be:Breathing control—participant to breathe at their usual rate and depthThoracic expansion—participant to breathe in slowly and deeply, pause for 1–2 s, breathe out fully but not forcefully. Repeated 2 to 3 times.Return to breathing control as aboveThoracic expansion exercises as above repeated 2–3 times.Return to breathing control as aboveFET—participant to take a slightly deeper breath than normal in, open mouth and keep it ‘O’ shaped, then breathe out more forcefully using abdominal muscles to assist. This breath out should sound like a forced sigh. Participants to repeat 2 to 3 times, with breathing control in between as needed.Return to breathing control until ready to begin another cycle.

The participant may cough if needed throughout the cycle and will be instructed to complete a minimum of three cycles each session, or until the end points listed below. Participants will be advised to complete the ACBT 3 times per day whilst in hospital, and then twice daily on hospital discharge for the full six months of the study duration.

#### Group 2: O-PEP therapy

The O-PEP therapy group will use an Aerobika® device. Participants will be instructed to complete O-PEP therapy according to guidelines [52], positioned in forward lean sitting with elbows supported on a table and feet flat on the ground (or upright in bed if unable to sit in a chair). The participants will be instructed to complete 10 breaths, followed by a huff, and then a cough only if needed, a minimum of 3 times per session, or until the end points listed below. Participants will be advised to use the O-PEP device 3 times per day whilst in hospital, and then twice daily on hospital discharge for the full six months of the study duration.

#### Group 3: Walking and FET (control condition)

Participants randomly assigned to group 3 will complete a standardised exercise program based on ground-based walking in combination with directed FET. Participants will self-select their walking speed to a modified Borg scale level of 3–5 whilst maintaining clinically acceptable, individually determined blood oxygen saturation levels and heart rate range parameters [53]. The goal will be to complete a total of 30 min/day; while they are inpatients, participants will be instructed to walk for 10 min, 3 times per day combined with a series of huffs at the end of each session. As outpatients, participants will be instructed to maintain the goal of 30 min/day in combination with FET. The FET involves a huff in combination with breathing control. A huff involves breathing out with mild-moderate force to aid clearance of sputum from the lungs [25]. The following instructions will be provided to participants:Huff—participant to take a slightly deeper breath than normal in, open mouth and keep it ‘O’ shaped, then breathe out more forcefully using abdominal muscles to assist. It should sound like a forced sigh. Participants to repeat 2 to 3 times with breathing control in between as needed.

Participants may cough as required during or following the intervention.

#### End points

The end points for the treatment sessions in all three groups will be:Two non-productive cycles plus clear huffTerminated by participant or physiotherapist for other reasons (such as participant fatigue, or the participant reporting subjectively feeling clear).Productive cough remaining, or huff not clear, but session reached maximum time of 30 min.

### Sample size

Sample size calculations were completed using G*Power software (version 3.1.9.6) to ensure the study was adequately powered. Based on previously published research, the minimal clinically important difference in sputum volume is 15 ml over 24 h [29]. To detect a difference at least as large as the minimal clinically important mean difference between groups, assuming a SD of 15 ml [29], power of 0.80 and alpha value of 0.05, 17 participants per group were required, giving a total of 51 participants required for the study. To accommodate a 40% attrition rate, 90 participants will be sought [29].

Due to the impact of COVID-19, rates of bronchiectasis exacerbations have reduced significantly in response to lock-down measures and the use of masks and social distancing in the community [54]. This reduction in exacerbation rates, and therefore hospitalisation rates, may impact rate of participant recruitment [54]. To minimise this impact, the time frame for participant recruitment will be continued as long as resources allow to maximise participant numbers. The sample size calculated allows for substantial attrition, and the authors acknowledge this may not be possible within resources constraints.

#### Statistical methods

Data analysis will be performed using SPSS V.28 (SPSS, Chicago, Illinois, USA). Data will be analysed using intention-to-treat principles, with alpha set at 0.05 for inferential analyses.

Data will be described as mean (standard deviation) or median (interquartile range) for continuous outcomes depending on distribution, and as frequency (percentage) for categorical outcomes. Demographic data, including age, pseudomonas aeruginosa colonisation, bronchiectasis severity scores and QoL-B scores will be compared to findings from the Australian Bronchiectasis Registry to determine external validity of the study findings. Where participants have a comorbid respiratory condition (such as Asthma or COPD), this will be noted and reported in the data analysis, and considered during interpretation of the findings of the study and when discussing the generalisability of findings.

The primary outcome, between-group difference in sputum volume over a 24-h period will be assessed using mixed-effects linear regression models, with treatment group and time included as main effects, and a group-by-time interaction term. Participant will be included as a random effect to account for the repeated measures nature of the data.

Secondary outcome measures with continuous outcomes will be analysed using linear regression, with binary outcomes using logistic regression, and with count outcomes using Poisson regression models. Repeated measures models will be used when appropriate. When data does not fit regression assumptions, non-parametric methods such as the Kruskal–Wallis test will be used to compare differences in scores on each instrument between groups at each of the different time points. Time-to-event outcomes, such as time to first recurrence of an exacerbation following discharge from initial hospital admission, will be visualised using Kaplan Meier survival curves and analysed using Cox proportional hazards regression.

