### Research aims

The primary aim of this randomised controlled trial is to compare the effects of the ACBT, O-PEP therapy and walking with huffing (control condition) on sputum expectoration for adults hospitalised with an acute exacerbation of bronchiectasis. Secondary aims are to compare the effects of these three interventions on HRQOL, health status, exacerbation rates and hospital admissions in a six-month period following this hospital admission.

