### Allocation

Participants will be randomly assigned to one of three groups, based on a computer-generated random sequence, with the allocation stratified by participant self-reported usual volume of sputum production (low volume (< 1 teaspoon sputum per day when well) or high volume (> 1 teaspoon sputum per day when well) [44]) to ensure a balance between groups in this characteristic. The computer-generated random allocations will be placed into numbered sequences (one for each strata) of opaque envelopes by the chief investigator, which will only be opened by the treating physiotherapist once baseline measures are completed. Only participants and treating physiotherapists will have knowledge of the group allocation. Blinding of assessors to treatment allocation will be achieved through the assessor not accessing medical documentation for the participant, participants being requested to place any handouts or equipment out of sight (e.g. in a drawer) prior to the assessor entering the room, and the participants being asked not to discuss any intervention with the assessor. The assessors will report any instances of unblinding and these will be recorded. The assessors will be senior cardiorespiratory physiotherapists who are not involved in the patient’s care during the admission.

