### Outcomes

All participants will be assessed at three time points during their hospital admission, and then once per month for six months post hospital discharge, by an assessor blinded to group allocation. The assessments to be conducted are described below. If participants withdraw from the study prior to completing the six months follow-up, their data will be included in data analysis up until the point of withdrawal unless specially requested otherwise by the participant.

The primary outcome of sputum volume, measured by the wet weight of sputum (grams), will be assessed three times during hospital admission on day 2, day 6, and within 24 h of hospital discharge. On each occasion, sputum will be collected during a physiotherapist-supervised ACT session, in the hour following the ACT treatment session, and over a 24-h period following the session. Twenty-four-hour sputum volume has been shown to be a responsive outcome measure during acute exacerbations of bronchiectasis [29, 43, 45]. Either an increase in sputum volume during the session, or one-hour post-session, or a decrease in sputum volume in the following 24-h period will be interpreted as an improvement in sputum clearance [29, 30, 43].

Secondary outcomes to be assessed include health status (Bronchiectasis Health Questionnaire) [46], disease-specific HRQOL (Quality of Life-Bronchiectasis questionnaire (QoL-B) and Leicester Cough Questionnaire) [47, 48] and exercise capacity (6 min walk test [49]). Each of these measures will be completed three times during hospital admission (on day 2, day 6, and within 24 h of hospital discharge). Additionally, health status and HRQOL will be assessed at two- and six-months post hospital discharge. Exercise capacity will be completed at six months post hospital discharge. The questionnaires will be completed via pen and paper during hospital admission, then via phone at two months post hospital discharge. At six months the questionnaires will be completed via paper and pen in the clinic or via phone if participants are unable to attend in person. The questionnaires for health status and HRQOL have been shown to be valid and reliable measures in individuals with bronchiectasis [46–48, 50].

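### The primary analysis compares three arms at three times at a flat 0.05 with no deciding contrast or gate; if arm pairs are tested as the sample size implies, the false-claim rate is about 12% to 32%, depending on how many are tested

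*Protocol article*

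**What the plan says.** All references are to the protocol article.

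- **Statistical methods, level.** One significance level is given, "with alpha set at 0.05 for inferential analyses". No split, ordering, gate or adjustment is stated.
- **Statistical methods, model.** The arms are compared on 24-h sputum by "mixed-effects linear regression models, with treatment group and time included as main effects, and a group-by-time interaction term"; repeated measurements are handled by a random effect for each person. No term or contrast is identified as the primary test.
- **Research aims.** The aim is to "compare the effects of the ACBT, O-PEP therapy and walking with huffing (control condition) on sputum expectoration". Walking is labelled the control, but no pair is given priority.
- **Allocation.** "Participants will be randomly assigned to one of three groups, based on a computer-generated random sequence".
- **Outcomes.** Sputum "will be assessed three times during hospital admission on day 2, day 6, and within 24 h of hospital discharge". None of the three is singled out.
- **Sample size.** A 15 ml difference between groups, SD 15 ml, power 0.80 and alpha 0.05 give 17 per group, 51 in total, raised to 90 for 40% attrition.

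**The concern.** Three arms make three pairs, and three collections make nine between-arm contrasts of 24-h sputum. Nothing ranks them, and each may be judged at the full 0.05. The sample size section points the same way: it gives full alpha to a pairwise difference in a trial that has three such pairs.

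The error at stake is a false ranking of techniques. The Discussion expects the results to guide physiotherapy practice and notes how little evidence there is on which technique to choose. If the three techniques are equivalent, the stated 5% should bound the chance of declaring one better. Whether it does depends on a rule that the article does not give.

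**Working it through.** **Step 1: reproduce the plan's own figure.** The standardised difference is d = 15/15 = 1. A two-sample t-test at two-sided 0.05 (noncentral t) has power 0.781 with 16 per group and 0.807 with 17, so 17 per group and 3 × 17 = 51 reproduce. A three-group F test does not give 17: it needs 16 per arm if two arms are equal and the third differs by 15 ml (power 0.814), or 21 per arm if the third mean lies midway (0.815). The stated number therefore belongs to one unadjusted pairwise test.

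**Step 2: count the contrasts.** 3 pairs × 3 times = 9. The independence formula, 1 − 0.95^9 = 0.37, does not apply because the contrasts share arms and participants. Simulation is needed.

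**Step 3: simulate with no true difference.** Inputs are three equal arms, 17 or 30 per arm (51/3 and 90/3), two-sided 0.05 tests, and equal correlation between a participant's three collections, which is the structure a random participant effect implies. The correlation is not in the article, so it is an assumption, shown over a range.

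Chance of at least one rejection among pairwise tests:

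| Contrasts tested | Correlation 0 | 0.5 | 0.9 |
|---|---|---|---|
| Nine, 17 per arm | 0.32 | 0.28 | 0.19 |
| Nine, 30 per arm | 0.32 | 0.29 | 0.20 |
| Three pairs at one time | 0.12 | 0.12 | 0.12 |

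Pooling the variance over times as well as arms lowers the nine-contrast figures slightly (0.27 at 17 per arm and correlation 0.5).

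Narrower families, at correlation 0.5:
- two technique-versus-control pairs at three times: 0.22;
- three pairs at two times, were day 2 treated as a baseline: about 0.20 to 0.22;
- two technique-versus-control pairs at one time: 0.09.

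**Step 4: the reading in which only model terms decide.** The model has a 2-df group test and a 4-df interaction test. At 17 per arm and correlation 0.5:
- either term taken alone: about 0.05;
- rejection by at least one of the two: about 0.10;
- contrasts opened after at least one of them rejects: about 0.08;
- contrasts opened only after the interaction rejects: about 0.03 to 0.04.

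**Step 5: check the proposed gate.** A 2-df group test at 0.05, followed by three pairs at 0.05 only on rejection, gives a family-wise rate of 0.05 when all arms are equal. When one arm differs, only one true null pair remains, and it is tested at 0.05 (simulated 0.05). This is why three arms need no further adjustment.

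**Step 6: power under the gate.** For a single collection, d = 1. For the average of three collections at correlation 0.5, the SD is 15 × √((1 + 2 × 0.5)/3) = 12.2 ml, so a constant 15 ml difference gives d = 15/12.2 = 1.22.

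| 17 per arm | Ungated | Gated, other two arms equal | Gated, third arm midway |
|---|---|---|---|
| Single collection | 0.81 | 0.77 | 0.70 |
| Average of three | 0.94 | 0.92 | 0.88 |

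At 30 per arm, gated power on a single collection stays at or above 0.93.

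**The case against.** The strongest reply is that this argues from silence. The article nowhere says that nine contrasts will be tested. It names one mixed model, and a reader could take its overall terms as the test, with pairs examined only afterwards; that keeps the rate at roughly 3% to 10%. Ordering and multiplicity rules often sit in an analysis plan, which is not shown. The family could also be smaller, since walking is consistently called the control.

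Much of this stands. A reader might infer that the trial carries a 28% false-positive rate instead of 5%. The documents do not support that as a fact: it needs an assumed correlation of 0.5 and all nine contrasts tested unadjusted, and the article states neither.

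The reply does not dispose of the point. The article itself fixes a flat 0.05 and sizes the trial on one pairwise difference, not on an overall test, so pairwise testing at full alpha is the reading its own arithmetic favours. On that reading, three pairs at one time already give 12%, with no correlation to assume. The Outcomes section also lets sputum during the session or in the following hour count as improvement. Those routes are left out of the count here and could only add to it.

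**Conclusion.** The point holds in a conditional form. The article combines a flat 0.05 and single-pair sizing with a three-arm, three-time primary comparison, and names no deciding term, pair, time or gate.

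If pairs are tested at 0.05, the chance of at least one false claim is about 12% for three pairs at one time and about 19% to 32% for all nine. The latter range rests on an assumed within-person correlation of 0.9 down to 0. If the overall terms alone decide, the rate is about 5% for one term and 8% to 10% if either counts. A plan whose error rate can run from 5% to about 30% according to an unstated choice should make that choice before the data are seen. This should be corrected; it does not invalidate the design.

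**What to change.** State in the Statistical methods:

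1. The primary test is one 2-df treatment-group test from the planned mixed model on 24-h sputum, averaged over the three planned collections (day 2, day 6, discharge), at two-sided 0.05. Defining it as the averaged contrast matters because, with an interaction in the model, the group coefficients otherwise depend on how time is coded.
2. The three arm pairs are tested on that same averaged contrast, each at 0.05, only if the primary test rejects.
3. The group-by-time term and the differences at each collection are reported as supportive estimates with 95% confidence intervals.

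The cost is a few sentences and no new data. Pairwise power falls a little: at 17 per arm, a constant 15 ml difference, SD 15 ml and assumed correlation 0.5, from about 0.94 to 0.92 (other two arms equal) or 0.88 (third arm midway). If a single collection were named instead, the fall would be from 0.81 to 0.77 or 0.70. A Bonferroni split over three pairs on a single collection (0.05/3 each) would cost more, leaving 0.65. Averaging also has a price: an effect confined to one collection is diluted, so the team should confirm that the average over the admission is the comparison they want.

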Number of exacerbations, number of hospital admissions and time to first exacerbation and hospital admission will be collected for six months post hospital discharge from the date of discharge. A blinded assessor will complete monthly phone calls using questions investigating clinical status in the last month including symptoms, hospital admissions and use of antibiotic therapy (and comparing participant responses to these questions to the international definition of an exacerbation for bronchiectasis [7]. Participants will also complete the Bronchiectasis Exacerbations and Symptoms Tool (BEST) daily from time of discharge from hospital to six month follow-up [51]. The BEST tool is a symptom diary, designed to detect bronchiectasis exacerbations, which involves six questions regarding breathlessness, sputum volume, cough, fatigue, sputum colour and cold and flu symptoms. It has been shown to be responsive to identifying exacerbations at onset and recovery for individuals with bronchiectasis [51].

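### Poisson regression is the only model named for the exacerbation and admission counts; its intervals are likely to be too narrow if counts are overdispersed, and the stated fallback does not suit event counts

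*Protocol article*

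**What the plan says.** Under Outcomes, the protocol article states: "Number of exacerbations, number of hospital admissions and time to first exacerbation and hospital admission will be collected for six months post hospital discharge". Research aims lists exacerbation rates and hospital admissions among the secondary aims, beside HRQOL and health status, without ranking them.

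Statistical methods gives one model for such data: "with count outcomes using Poisson regression models". It names no negative binomial alternative, robust or scaled standard error, or follow-up offset for counts. Two general provisions follow. One is "Repeated measures models will be used when appropriate". The other is a fallback: "When data does not fit regression assumptions, non-parametric methods such as the Kruskal–Wallis test will be used to compare differences in scores on each instrument", comparing groups at each time point. First events are to be analysed separately by Kaplan–Meier curves and Cox regression.

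Two other statements bear on observation time. For participants who withdraw early, Outcomes says "their data will be included in data analysis up until the point of withdrawal unless specially requested otherwise by the participant". Sample size says "To accommodate a 40% attrition rate, 90 participants will be sought".

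**The concern.** A Poisson model fits one rate per group and derives its standard errors from the mean alone. If participants within a group differ in underlying risk, the variance of their counts exceeds the mean and those standard errors are too small.

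The article gives good reason to expect such differences. Participants sets no severity limit and does not exclude people with a recent admission or exacerbation. The baseline assessment scores severity on an index, and growth of organisms such as Pseudomonas is recorded during the admission. Statistical methods anticipates comorbid asthma or COPD.

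At stake is the reliability of the p-values and intervals for exacerbation and admission counts. A chance difference between techniques could be reported as a real one, in results that the Discussion expects to inform prescribing of techniques after discharge.

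A second, smaller matter is observation time. Keeping data up to withdrawal means that participants will be observed for different lengths of time, and a comparison of rates has to allow for that.

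**Working it through.** **The plan's own figure.** The only sample-size calculation is for 24-h sputum: difference 15 ml, SD 15 ml, so d = 15/15 = 1. A two-sample t-test (two-sided 0.05 assumed) with 17 per group has power 0.807; 16 per group gives 0.781. So 17 per group and 51 in total reproduce. For attrition, 51/0.6 = 85, and 90 is a round-up (90 × 0.6 = 54). Nothing below alters this. The article gives no event rate, dispersion or power for the counts.

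**Inputs for the check.** From the article: 90 participants in three groups, taken as 30 per arm; six months of follow-up; alpha 0.05. Assumed: mean count μ of 0.5, 1 or 1.5 per six months, and individual rates that vary as a gamma distribution with mean 1 and variance k of 0, 0.5 or 1.

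**Interval width.** Under this model Var(Y) = μ(1 + kμ), while Poisson assumes μ. Hence

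- true SE / Poisson SE = √(1 + kμ)
- actual coverage of a nominal 95% interval = 2Φ(1.96/√(1 + kμ)) − 1

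| μ | k | 1 + kμ | SE ratio | Coverage |
|---|---|---|---|---|
| 0.5 | 0.5 | 1.25 | 1.12 | 92% |
| 0.5 | 1 | 1.50 | 1.22 | 89% |
| 1 | 0.5 | 1.50 | 1.22 | 89% |
| 1 | 1 | 2.00 | 1.41 | 83% |
| 1.5 | 0.5 | 1.75 | 1.32 | 86% |
| 1.5 | 1 | 2.50 | 1.58 | 79% |

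With k = 0 the ratio is 1 and coverage is nominal.

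**Simulation.** Two arms of 30, true rate ratio 1, 40% dropout in each arm spread evenly over six months, 40,000 replicates per scenario:

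- Poisson with offset, k = 0: type I error 0.041 to 0.048.
- Poisson with offset, k = 0.5 or 1: 0.065 (μ 0.5, k 0.5) to 0.197 (μ 1.5, k 1).
- Poisson with offset and robust SE, all of these scenarios: 0.047 to 0.064.

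Negative binomial regression was not simulated.

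**Follow-up time.** If a fraction d drops out evenly over six months, mean observed time is 1 − d/2 of the full period. Without an offset, a true ratio of 1 is estimated as the ratio of these fractions:

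- 40% v 40%: 0.80/0.80 = 1.00, no bias.
- 30% v 50%: 0.75/0.85 = 0.88 (simulated 0.876; with offset about 0.995).
- 20% v 60%: 0.70/0.90 = 0.78 (simulated 0.772; with offset 0.995).

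The arm-specific dropout figures are illustrative; the article gives none.

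**The case against.** The strongest reply is that a journal article condenses the plan. An offset is the kind of detail commonly left to an analysis plan, Poisson regression accommodates one readily, and the stated aim already speaks of rates. That stands. A reader might infer that the plan ignores follow-up time, so that one event-free month counts the same as six, but the text never says an offset will be left out. The offset is therefore a recommendation here, not an error found.

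A reader might also infer that 40% attrition will bias the rates. It need not. The ratio is distorted only if dropout differs between arms or is related to outcome. The 40% is also an allowance attached to the sputum sample size, not a forecast or ceiling for the six-month counts.

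On dispersion, the reply is that the article quantifies none, and that recurrent events alone do not imply a variance above the mean. This also stands: it would be too strong to say that intervals will be too narrow or that false positives will exceed 5%. The case rests on the mixed population and on assumed values.

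The fallback is a weaker defence. It is worded for instrument scores at time points. A Kruskal–Wallis test on event counts gives no rate ratio and makes no allowance for follow-up. The repeated-measures provision is not tied to a six-month total per participant. The Cox analyses do handle censoring and do not need the Poisson variance, but they cover first events only.

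Finally, nothing in the article makes these counts the main long-term aim.

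**Conclusion.** The point holds in conditional form. The one model named for counts fixes the variance at the mean, in a population likely to be more variable than that, and the fallback does not repair it. Under the assumed range, true standard errors are 1.12 to 1.58 times the model's and nominal 95% intervals cover about 92% down to 79%. If there is no overdispersion, there is no under-coverage.

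The follow-up element is a safeguard. It matters if dropout differs between arms, where an assumed 30% v 50% would turn a true ratio of 1 into about 0.88. It does not affect the ratio if dropout is equal.

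Only secondary outcomes are concerned. The change is worth making before the data are analysed.

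**What to change.** State that numbers of exacerbations and admissions will be analysed by negative binomial regression, or by Poisson regression with robust standard errors. Include log observed follow-up time from discharge as an offset, adjust for the sputum-volume randomisation stratum, and report rate ratios with 95% CIs. Confine the Kruskal–Wallis fallback to the instrument scores for which it is worded.

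The stratum term reflects the stratified allocation; it cures neither overdispersion nor unequal follow-up. The offset corrects for unequal observation time, but not for withdrawal that depends on a participant's own exacerbation risk.

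The cost is a sentence or two of analysis wording and somewhat wider intervals. On the log scale they widen by the SE ratios in the table if counts are overdispersed as assumed. If they are not, little is lost: with k = 0 the offset-and-robust analysis had type I error of 0.047 to 0.054. No change to the sample size or primary analysis is needed.
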